## 5.6 Discontinuation of Therapy

Protocol treatment will be discontinued for any of the following reasons:

- Any dose-limiting toxicity as defined in [Section 8.9](#).
- Disease progression requiring other therapy (e.g. surgery under general anesthesia, radiation, chemotherapy, or steroid therapy). The appearance of small metastases or recurrent tumor deposits will not be a basis for discontinuing the study treatment. Biopsy to determine the nature of new lesions or minor surgical procedures to excise a new lesion (with or without anesthesia) will not be a basis for discontinuing study treatment.
- Initiation of cytotoxic chemotherapy, radiation therapy, surgery for resection of disease, steroid therapy, or other immunosuppressive therapy.
- Any other potential adverse reaction deemed sufficiently serious to warrant discontinuation of therapy by the Principal Investigator or one of the Associate Investigators.

- Noncompliance with the requirements of the study.
- Therapy may be discontinued at the participant's request.
- Therapy may be discontinued at the discretion of an Investigator.
- Pregnancy. Pregnant participants will continue to be followed for the duration of the pregnancy.

Participants who discontinue treatment will be followed according to the follow-up schedule outlined in [Section 9.1](#), unless a participant has withdrawn consent.

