### **3.2 Exclusion Criteria**

- 1) Participants who have received the following medications or treatments at any time within 4 weeks of registration:
- Chemotherapy
  - Interferon (e.g. Intron-A®)
  - Radiation therapy (Stereotactic radiotherapy, such as gamma knife, can be used  $\geq 1$  week and  $\leq 6$  months prior to registration)
  - Allergy desensitization injections
  - High doses of systemic corticosteroids, with the following qualifications and exceptions:
    - In patients with adrenal or pituitary insufficiency replacement steroid doses are allowed; however, daily doses of 10 mg or more of prednisone (or equivalent) per day administered

- parenterally or orally are not allowed in patients with normal adrenal and pituitary function.
- Inhaled steroids (e.g.: Advair®, Flovent®, Azmacort®) are permitted at low doses (less than 500 mcg fluticasone per day, or equivalent) .
  - Topical, nasal, and intra-articular corticosteroids are acceptable.
  - Growth factors (e.g. Procrit®, Aranesp®, Neulasta®)
  - Interleukins (e.g. Proleukin®)
  - Any investigational medication
  - Targeted therapies specific for mutated BRAF or for MEK
- 2) Participants who are currently receiving nitrosoureas or who have received this therapy within 6 weeks of registration.
  - 3) Participants who are currently receiving a checkpoint molecule blockade therapy, or who have received this therapy within 12 weeks of registration.
  - 4) Participants with known or suspected allergies to any component of the vaccine.
  - 5) Participants who were vaccinated previously with 6MHP are excluded. Participants who have received vaccinations containing agents other than the synthetic peptides included in this protocol and have recurred during or after administration of the vaccine will be eligible to enroll 12 weeks following their last vaccination.
  - 6) Participants who have previously received CDX-1127 or other CD27 agonistic antibody.
  - 7) Pregnancy. Female participants of childbearing potential must have a negative pregnancy test (urinary or serum beta-HCG) obtained within 2 weeks prior to registration. Males and females must agree, in the consent form, to use effective birth control methods during the course of active study treatment and for up to 70 days after the last dose of study treatment.
  - 8) HIV positivity or evidence of active Hepatitis C virus (testing to be done within 6 months of study entry).

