#### 5.3.3 Pre-medications

Prophylactic premedication will not be given initially; however, if a patient experiences a grade 2 infusion related reaction, that patient should be pre-medicated for subsequent infusions with diphenhydramine 50 mg (or equivalent) and/or 500 to 750 mg paracetamol (acetaminophen) at least 30 minutes prior to CDX-1127 administrations. Should 2 or more patients develop  $\geq$  Grade 2 symptoms, these prophylactic pre-medications are recommended for future infusions in all subsequent patients. Prophylactic premedication with corticosteroids may also be added if clinically indicated.

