### **5.9 Permitted Medications or Treatments**

- Nonsteroidal anti-inflammatory agents
- Anti-histamines (e.g. Claritin®, Allegra®)
- Topical corticosteroids (refer to Exclusion Criteria for permitted steroids)
- Steroid treatment for infusion reactions
- Replacement steroids for adrenal insufficiency
- Short-term therapy for acute conditions not specifically related to melanoma
- Chronic medications except those listed in [Section 5.8](#)
- Non-live vaccines, including non-live influenza vaccines, are permitted, but should be administered at least 2 weeks prior to or at least 2 weeks after a

study drug. Live vaccines should not be administered within 30 days of registration or within 30 days after the last dose of study drug.

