- Stop the CDX-1127 infusion, begin an i.v. infusion of normal saline, and treat the subject with diphenhydramine 50 mg i.v. (or equivalent) and/or 500 to 750 mg paracetamol/acetaminophen; remain at bedside and monitor subject until resolution of symptoms. Corticosteroid therapy may also be administered per investigator judgment. If the infusion is interrupted, then restart the infusion at 50% of the original infusion rate when symptoms resolve; if no further complications ensue after 30 minutes, the rate may be increased to 100% of the original infusion rate. Monitor subject closely. If symptoms recur then no further CDX-1127 will be administered at that visit. The amount of study drug infused must be recorded on the case report form (CRF). Subjects who experience an adverse event, including an infusion reaction of Grade 2, during the post-infusion observation period that does not resolve during this time should be observed for 24 hours or until the adverse event resolves with vital sign measurements every 4 hours and additional evaluations as medically indicated for the management of the adverse event.

**For Grade 3 or Grade 4 symptoms:** (Grade 3: prolonged [i.e., not rapidly responsive to symptomatic medication and/or brief interruption of infusion]; recurrence of symptoms following initial improvement; hospitalization indicated for other clinical sequelae [e.g., renal impairment, pulmonary infiltrates]. Grade 4: life-threatening consequences; urgent intervention indicated).

- Immediately discontinue infusion of CDX-1127. Begin an i.v. infusion of normal saline, and treat the subject -per investigator judgment. Subjects who experience an adverse event, including an infusion reaction of Grade  $\geq 3$ , regardless of resolution, may be observed for up to 24 additional hours, based on the investigator's judgment. Restarting the infusion, and subsequent retreatment will be at the discretion of the investigator.

In the case of late-occurring hypersensitivity symptoms (e.g., appearance of a localized or generalized pruritus within 1 week after treatment), symptomatic treatment may be given (e.g., oral antihistamine, or corticosteroids).

Investigators may follow their institutional guidelines for the treatment of anaphylaxis.

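### Section 5.6 makes any steroid therapy a mandatory reason to stop, but Sections 3.2 (via 5.8), 5.3.3, 5.9 and 5.10 allow several steroid uses during treatment; both arms are affected, Arm A more

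*Combined protocol and SAP*

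**What the plan says.** Section 5.6 opens with "Protocol treatment will be discontinued for any of the following reasons", so the list is mandatory and any one entry is enough. One entry reads "Initiation of cytotoxic chemotherapy, radiation therapy, surgery for resection of disease, steroid therapy, or other immunosuppressive therapy". It stands apart from the entry on disease progression and refers to no other section.

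Other sections treat steroids differently:

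- **Section 3.2**, an entry criterion, bars "daily doses of 10 mg or more of prednisone (or equivalent) per day administered" by mouth or injection when adrenal and pituitary function are normal. It also says "In patients with adrenal or pituitary insufficiency replacement steroid doses are allowed" and "Topical, nasal, and intra-articular corticosteroids are acceptable", and it permits low-dose inhaled steroids.
- **Section 5.8** carries the 3.2 rule into the treatment period and adds the exceptions in 5.10.
- **Section 5.9** lists "Steroid treatment for infusion reactions" among permitted treatments, along with topical steroids and replacement steroids for adrenal insufficiency.
- **Section 5.3.3**, on premedication for CDX-1127 after an infusion reaction, says "Prophylactic premedication with corticosteroids may also be added if clinically indicated".
- **Section 5.10**, on Grade 2 infusion reactions, says "Corticosteroid therapy may also be administered per investigator judgment" and then describes restarting the interrupted infusion once symptoms resolve. It also allows corticosteroids for late hypersensitivity symptoms.

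**The concern.** Two sites could follow the protocol faithfully and handle the same participant in opposite ways. Suppose an Arm A participant has a Grade 2 infusion reaction that is not a DLT and is given a corticosteroid. Under 5.10 and 5.3.3 that participant restarts and may be premedicated for later infusions. Under 5.6 read literally, protocol treatment ends.

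This matters beyond site confusion because the two paths lead to different data. A participant who continues has research blood drawn on days 127 and 176. One who is discontinued follows the end-of-treatment and follow-up calendar in Section 9.1, where research blood is drawn only at the two end-of-treatment visits. The primary immunogenicity endpoint needs the later samples. The trial is open-label, multi-center and planned at 15 participants per arm, so a few losses that depend on how a site reads 5.6, with an extra route to loss in one arm, would bear on the estimated difference.

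**Working it through.** **1. Allowances set against the 5.6 item, by arm**

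| Steroid use | Allowed in | Arms affected | Conflict with 5.6 |
|---|---|---|---|
| Systemic, below the 3.2 threshold | 3.2 via 5.8 (not barred) | A and B | Yes on a literal reading |
| Low-dose inhaled | 3.2 via 5.8 | A and B | Yes on a literal reading; eased if 5.6 means immunosuppressive treatment |
| Topical, nasal, intra-articular | 3.2 via 5.8; topical also in 5.9 | A and B | As above |
| Replacement | 3.2 via 5.8; 5.9 | A and B | As above |
| Premedication before an infusion | 5.3.3 | A only | Yes on either reading, unless 5.3.3 is taken to override |
| Treatment of an infusion reaction | 5.9, 5.10 | A only | Same |
| Late hypersensitivity | 5.10 | A only | Same |

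The last three rows are confined to Arm A because Section 5.3.1 gives CDX-1127 to Arm A only. The first four carry no arm restriction.

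**2. Path to the primary endpoint**

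- Infusions are on days 1, 36 and 78 (5.3.1), all before day 127, so a stop prompted by one can precede the first persistence sample.
- Section 7.1.2 counts a participant as evaluable for the primary endpoint on one of three grounds: immune response assessed at baseline and at least day 127, progression before day 127, or a stop for DLTs. A steroid-triggered stop without progression or a DLT meets none of them once the day 127 sample is missing.
- The 7.1.2 failure rule covers only progression and DLT stops, so such a participant is not counted as a failure either.

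**3. Size of one loss**

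1/15 = 0.067, or 6.7 percentage points of an arm's rate.

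**4. How many**

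The documents give no rate of steroid use. Section 1.6.4 calls infusion reactions rare with monotherapy and infrequent with checkpoint antibodies. As an assumption only, take 5% to 15% of about 17 Arm A participants (34/2): 17 × 0.05 = 0.85 and 17 × 0.15 = 2.55, so roughly 1 to 3 people. That range covers all infusion reactions. Non-DLT reactions treated with steroids are a subset, so it is closer to an upper range.

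**5. Sensitivity of the Section 7.2 criterion (illustration)**

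Section 7.2 looks for a positive lower 90% bound on the difference in persistent response, by the Miettinen and Nurminen score method. The limits are the values d that solve

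(p1 − p2 − d) / sqrt{ [ q1(1 − q1)/n1 + q2(1 − q2)/n2 ] × N/(N − 1) } = ±1.645,

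where p1 and p2 are the observed rates, q1 and q2 are the maximum-likelihood rates constrained to differ by d, and N = n1 + n2. The difference is CDX-1127 arm minus vaccine-alone arm, and one Arm A participant is removed.

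| Full table (A vs B) | Lower bound | After the loss | Lower bound |
|---|---|---|---|
| 6/15 vs 2/15 | −0.4% | 6/14 vs 2/15 (non-responder lost) | +1.8% |
| 6/15 vs 2/15 | −0.4% | 5/14 vs 2/15 (responder lost) | −4.4% |
| 7/15 vs 2/15 | +5.6% | 7/14 vs 2/15 (non-responder lost) | +8.2% |
| 6/15 vs 3/15 | −8.1% | 6/14 vs 3/15 (non-responder lost) | −6.0% |

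Only the first row changes sign. One loss moves the lower bound by about 2 to 4 percentage points.

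**The case against.** The strongest reply is that the sections can be read together. The 5.6 entry groups steroids with chemotherapy, radiation and resection and closes with other immunosuppressive treatment, and the progression entry before it uses the same steroid term for treatment of recurrent disease. On that reading topical, inhaled and replacement steroids fall outside 5.6. A site would also probably let the specific permissions in 5.8 to 5.10 prevail over a general list, which leaves only a missing cross-reference. This stands in part. It eases the local and replacement conflicts in both arms. It does not clearly settle systemic corticosteroids given for an infusion reaction or as premedication, because nothing in 5.6 yields to those sections.

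Three further objections hold:

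- The protocol recognises stopping one drug while the other continues (5.5.1 and the EOT 1 column in 9.1), so 5.6 need not end the vaccine as well as CDX-1127. It does not say which is meant.
- Some steroid-treated reactions would be DLTs under Section 8.9, for example allergic reactions of Grade 2 or higher. Those participants stay evaluable, as failures.
- The absence of later samples and of a failure rule is not peculiar to steroids. Stops for noncompliance, participant request or investigator discretion have the same effect.

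A reader might infer that only Arm A faces contradictory rules. The documents do not support that: the 3.2 threshold, carried in by 5.8, and the local and replacement allowances apply in both arms. A reader might also infer from the first row of the sensitivity table that the wording would reverse the trial's conclusion. That is one selected case. Losing a responder moves the bound the other way, the neighbouring tables keep their sign, and Section 7.5 describes the study as estimating differences rather than testing them.

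**Conclusion.** The contradiction is real and is an internal inconsistency: a mandatory stopping item without limits stands against four sections that, directly or by reference, let treatment continue with some steroid use. It reaches both arms, with additional conflicts in Arm A from infusion reactions and premedication.

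The effect on the primary endpoint is possible but small. It requires a steroid-treated event before day 127 that is neither a DLT nor followed by progression before that day, at a site that applies 5.6 literally and moves the participant off the active-treatment calendar. Each such loss is worth 6.7 percentage points of a 15-person arm, in either direction depending on who is lost. The number of losses cannot be computed from the documents. No view is taken on which steroid rule is clinically right.

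**What to change.** Reconcile the steroid item in 5.6 with 3.2, 5.3.3, 5.8, 5.9 and 5.10, so that one rule, with whatever dose, route and indication limits the sponsor sets, decides whether treatment continues after steroid use. Have 5.6 refer to that rule instead of naming steroids without qualification, and state whether a stop under it applies to one study drug or to all.

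The cost is a clarifying sentence and cross-reference through a minor amendment or site memo. It adds no procedures, visits or samples.

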### 5.5 Dose Delays

#### 5.5.1 Dose Delays Due to Toxicity

- Dose delays for vaccines and CDX-1127

In circumstances where assessment of an AE is limited, such as by intercurrent illness, or when laboratory studies are required to assess for other causes of toxicity, the vaccine\* and/or CDX-1127 schedule may be interrupted for up to 21 days.

- If a toxicity can be clearly attributed to either the vaccine or CDX-1127, then only the investigational drug that caused the toxicity will be delayed.
- One vaccine and/or one CDX-1127 delay up to 21 days is allowed if due to an AE, regardless of attribution.
- If there is more than one vaccine and/or one CDX-1127 delay by 7 days or more due to an AE, regardless of attribution, the investigational drug that caused the toxicity should be discontinued. The remaining investigational drug may be continued.
- Missed doses may be shifted. Participants who are treated outside of the established schedule should return to the original schedule as soon as possible, keeping in mind that there must be at least a minimum of 6 days in between CDX-1127 infusions and a minimum of 5 days in between vaccines.

\*The vaccine includes all components that make up the vaccine (e.g.6MHP + Montanide ISA-51 with or without).

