### **5.13 Biopsies**

#### Vaccine Site Biopsies

Before Protocol v12-03-2020, each participant had a biopsy of a vaccine site at two time points (days 22 and 85 or End of Treatment). After approval of Protocol v12-03-2020, only the biopsy at day 22 will be done. The biopsy will consist of three 4-mm punch biopsies of skin.

Prior to Protocol v12-03-2020, the vaccine site biopsy at day 85 was required for all participants, except that it was optional for participants who discontinued vaccine therapy before vaccine 6 but did not discontinue varilumab therapy if applicable, and it should not have been done if the participant had ulceration at the vaccine site or had a vaccine-site related DLT.

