#### 8.4.2 Time Span for Reporting Adverse Events

Reporting of AEs will begin when the participant is first administered the study drug or has a study related procedure. Events occurring through 30 days after administration of the last dose of vaccine or varlilumab, regardless of attribution, will be reported. Participants are to be contacted 30 days after receiving study drug to obtain adverse event data. This may be done by phone, mail, email, or in person. For patients who discontinue protocol therapy prior to day 176, they should be contacted 30 days after the last vaccine or varlilumab administration for completion of AE data collection.

AEs should be followed to resolution or stabilization. If an AE worsens and becomes an SAE, it should be reported as serious per the guidelines specified for SAE reporting.

AEs that are possibly, probably, or definitely related to any of the study drugs will be recorded until the participant completes treatment follow-up. If, during treatment follow-up, the participant receives an alternative anti-cancer treatment, participants will be off treatment follow-up and will be followed yearly for disease progression and survival.

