m If the day 176 visit is delayed, the day 183 visit needs to be 7 days later than the day 176 visit. The range of days in the delayed visit table ([Table 7](#)) applies around the 7 day interval.

n Vaccines 5 and 6 (days 57 and 78) will not be administered after approval of Protocol v12-03-2020.

| Studies & Tests                                             | End of Treatment (EOT)                                              |                                                           | Follow-Up                                                    |                    |
|-------------------------------------------------------------|---------------------------------------------------------------------|-----------------------------------------------------------|--------------------------------------------------------------|--------------------|
|                                                             | EOT 1 c                                                  | EOT 2                                                     | Follow-up Discontinuation of study drugs a (FUV1) | Survival Follow-up |
|                                                             | Premature discontinuation of one study drug and/ or all study drugs | 7 days post premature discontinuation of vaccine at EOT 1 | 30 days post discontinuation                                 | Annually           |
| CBC with differential                                       | X                                                                   | X                                                         |                                                              |                    |
| Comprehensive chemistry                                     | X                                                                   | X                                                         |                                                              |                    |
| Urinalysis                                                  | X                                                                   |                                                           |                                                              |                    |

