| Anti-nuclear antibody / Rf                                  | X                                                                   |                                                           |                                                              |                    |
| Participant diary reviewed and/or distributed               | X                                                                   | X                                                         | X                                                            |                    |
| Survival                                                    |                                                                     |                                                           |                                                              |                    |
| Survival Status                                             |                                                                     |                                                           |                                                              | X                  |
| Start of Antineoplastic therapy                             |                                                                     |                                                           |                                                              | X                  |

a Patients are to be contacted 30 days after the last administration of study drug to obtain adverse event data. This may be done by phone, mail, email, or in person.

b Subjects may be contacted by telephone for survival follow-up status. The expectation is that there will be additional follow-up as part of standard of care, either by the study physician or by a local referring physician. Every effort will be made to obtain data on disease status and survival at all such visits, in addition to the mandated study visits.

c If a subject is discontinued and the assessments have been completed as part of a regularly scheduled visit within 7 days, the assessments do not need to be repeated.

d If a subject has had research bloods drawn ≥6 days after the last administered vaccine, the research bloods do not need to be drawn again.

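### Participants who stop treatment without DLT or progression move to a follow-up calendar with no day 127 or 176 research blood, so the primary endpoint goes unmeasured, possibly unequally by arm

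*Combined protocol and SAP*

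**What the plan says.** **After stopping.** Section 5.6: "Participants who discontinue treatment will be followed according to the follow-up schedule outlined in" Section 9.1, unless consent has been withdrawn. In the follow-up calendar of 9.1, EOT 1 is headed "Premature discontinuation of one study drug and/ or all study drugs" and EOT 2 "7 days post premature discontinuation of vaccine at EOT 1". Research blood is marked at these two visits only, and the EOT 2 draw can be skipped: "If a subject has had research bloods drawn ≥6 days after the last administered vaccine", it need not be repeated. After that come a 30-day contact and annual survival follow-up, neither with research blood.

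**The primary endpoint.** Section 7.1.2 defines pRsp as a durable response plus a response on day 127 or 176. A participant is evaluable if assessed at baseline and at least day 127, or if they progressed before day 127, or stopped for DLT. The last two groups are scored as failures without a sample. No rule covers other participants without a day 127 sample.

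**Stopping one drug.** Section 5.5.1 says that after more than one delay of 7 days or more for an adverse event, "the investigational drug that caused the toxicity should be discontinued. The remaining investigational drug may be continued". By Table 9 only Arm A has a second investigational drug, CDX-1127, given on days 1, 36 and 78 (Section 5.3.1).

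**The concern.** A participant who stops early without DLT or progression may still be a persistent responder. Both active-treatment calendars draw research blood on days 15, 22 and 36, so a durable response can already be on record. Whether it persisted depends on a draw that the follow-up calendar does not contain. The participant then leaves the evaluable set for a reason that may be related to treatment.

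The loss may also be unequal. In Arm B, stopping vaccine means stopping all study drug, so 5.6 applies in full. In Arm A, a participant who stops vaccine and continues CDX-1127 has not plainly discontinued treatment and may stay on the active calendar, which includes days 127 and 176. With about 15 evaluable participants per arm and a decision that turns on whether the 90% interval for the difference in pRsp lies above zero, one to three such losses can matter.

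**Working it through.** **1. The plan's own figures (Section 7.2).** Enrolment: 30/0.90 = 33.3, rounded up to 34, as stated. Reference rate: 5/38, exact 90% interval 5.33% to 25.70%, half-width 10.18%, as stated. Difference needed with 15 per arm for a lower 90% bound of zero: 27.0 points at a 13.1% control rate and 30.0 points at 25.7%, within about one point of the stated 28% to 31%. No stated figure is wrong.

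**2. Who is affected.**

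| Reason for stopping | Handling in 7.1.2 | Sample needed? |
|---|---|---|
| DLT | failure, both arms | no |
| Progression before day 127 | failure, both arms | no |
| Second adverse-event delay under 5.5.1; participant or investigator choice | none given | yes, day 127 |

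Only the last row loses the endpoint. The documents give no count for it.

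**3. Sensitivity of the decision.** Differences are Arm A minus Arm B, with Arm B as vaccine alone (Table 9). The Miettinen-Nurminen statistic at a difference d is

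z(d) = (pA - pB - d) / sqrt{[qA(1-qA)/nA + qB(1-qB)/nB] x N/(N-1)},

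where qA and qB are the estimates constrained to differ by d. The lower 90% bound is the d at which z(d) = 1.645. At d = 0 both constrained estimates equal the pooled rate, so the sign of the bound can be checked by hand. For 6/15 versus 2/15 the pooled rate is 8/30 = 0.267; the variance is 0.267 x 0.733 x (2/15) x (30/29) = 0.0270; z(0) = 0.267/0.164 = 1.62. This is below 1.645, so the bound is below zero.

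| Assumed result | Difference | z(0) | 90% interval |
|---|---|---|---|
| 6/15 vs 2/15 | 26.7% | 1.62 | -0.4% to 50.9% |
| one B responder unsampled: 6/15 vs 1/14 | 32.9% | 2.03 | 7.0% to 55.8% |
| 8/15 vs 3/15 | 33.3% | 1.86 | 4.0% to 57.6% |
| two B non-responders unsampled: 8/15 vs 3/13 | 30.3% | 1.61 | -0.8% to 55.7% |
| 7/15 vs 2/15 | 33.3% | 1.96 | 5.6% to 57.0% |
| three B non-responders unsampled: 7/15 vs 2/12 | 30.0% | 1.61 | -0.6% to 55.0% |

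**4. Average shift.** Assume a share q of Arm B is unsampled, all of them non-responders, and Arm A is fully sampled. The Arm B evaluable rate becomes p/(1-q). For q from 5% to 20%, the A minus B difference moves by -0.7 to -3.3 points at p = 13.1% (for example 0.131 - 0.131/0.80 = -0.033) and by -1.4 to -6.4 points at p = 25.7%. If unsampled participants would have responded, the shift goes the other way. The values of q are assumptions.

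**The case against.** **The arm difference is inferred.** A reader might infer that the plan samples Arm A vaccine-stoppers on days 127 and 176 and leaves Arm B vaccine-stoppers unsampled. The text does not establish this. EOT 1 and EOT 2 are not limited by arm, so an Arm A vaccine-stopper enters them too. CDX-1127 ends on day 78 and cannot by itself keep anyone on the calendar to day 127. Arm A footnote l places a vaccine-stopper still on CDX-1127 at day 85, but Arm B footnote k contemplates vaccine-stoppers there as well. Section 5.13, on those who "discontinued vaccine therapy before vaccine 6 but did not discontinue varilumab therapy if applicable", can accommodate both arms. All three texts concern the day 85 biopsy, since removed, and none mentions later blood. Section 5.1 can also be read as keeping participants on the calendar through 6 months. This objection stands: the documents leave the question open and do not settle it against Arm B.

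**The group is small.** DLT and pre-day-127 progression stops are handled alike in both arms. Table 7 footnote a, on delays for reasons other than toxicity, ends protocol treatment in both arms. With pre-booster vaccines now on days 1, 8, 15 and 36 only, there are few chances for two delays. This stands as a limit on size.

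**The numerical cases are chosen near the threshold.** This also stands. For example, 7/15 versus 2/15 keeps a positive lower bound after one non-responder is lost (2/14, +3.8%) or two (2/13, +1.7%).

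**Two further inferences fail.** One is that related adverse events in early stoppers go uncollected, because "AEs that are possibly, probably, or definitely related to any of the study drugs will be recorded until the participant completes treatment follow-up" while the calendar's last toxicity check is at 30 days. Section 8.4.2 itself sets the 30-day contact as the completion of adverse-event collection for those who discontinue before day 176. The other is that no analysis rule could give these participants an outcome. Section 7.1.2 already assigns failure without a sample to two groups, and a similar rule could be written here. It would define an outcome but would not measure persistence.

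**Conclusion.** The point holds in a limited form. Under 5.6 and 9.1 as written, a participant who stops all treatment for a reason other than DLT or progression before day 127 has no scheduled day 127 or 176 research blood and is non-evaluable for pRsp. Because only Arm A has a second drug to continue, the loss can fall unevenly, but that is a plausible reading of an ambiguous text and not a stated rule. Neither the frequency nor the direction of bias can be derived from the documents. The calculations assume 15 evaluable per arm, full sampling in Arm A and one to three unsampled participants in Arm B. They show that so few losses can move a result across zero in either direction when it lies near the threshold. The 10% allowance in 7.2 can replace numbers, but it does not remove selective loss.

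**What to change.** In Section 5.6 and the follow-up calendar of 9.1, state that in both arms a consenting participant who stops one or all study drugs without DLT or progression, and has not started another anticancer therapy, keeps the already scheduled day 85, 127 and 176 research blood draws, in addition to EOT 1 and EOT 2. The limit on other therapy matches 5.1, which ends treatment follow-up at that point, and avoids attributing to the study drugs a response that reflects a new treatment. Reconcile 5.5.1, 5.6, 7.1.2 and calendar footnotes k and l with this rule, including how 7.1.2 counts those who still lack a sample.

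The cost is one sentence and a calendar footnote. A few participants off treatment return for two or three blood draws that are already in the study calendar, and some will decline.
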